**Methods/design:**

One hundred tobacco users with mental illness who were part of an outpatient mental health program in Nairobi, Kenya were recruited and allocated into intervention and control groups of the study (50 users in intervention group and 50 users in control group). Participants allocated to the intervention group were invited to participate in 1 of 5 tobacco cessation groups. The intervention group received the 5As (Ask, Advise, Assess, Assist and Arrange) and tobacco cessation group behavioral intervention, which included strategies to manage cravings and withdrawal, stress and anxiety, and coping with depression due to withdrawal; assertiveness training and anger management; reasons to quit, benefits of quitting and different ways of quitting. Individuals allocated to the control group received usual care. The primary outcome was tobacco cessation at 24 weeks, measured through cotinine strips. Secondary outcomes included number of quit attempts and health-related quality of life.

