### Baseline and follow-up assessments

During baseline, Age of first use, duration of use, amount used, mental illness managed, Fagerstrom test score, and other substances used were documented. During weeks 4, 12 and 26, Quit attempts made, amount currently being smoked and Cotinine test results were documented. During week 26, the WHOQOL questionnaire was re-administered.

Based on previous tobacco cessation intervention trials, it was assumed that those who did not report abstinence had positive cotinine results.

At the group assessments (Weeks 4, 12, and 26), participants who reported continued tobacco use abstinence and consented to a saliva test were tested using a nicotine cotinine strip (Devon Medical: Nicotine/tobacco test kit). The saliva tests were evaluated by the nurses working at the hospital who were blinded to treatment allocation and were not otherwise part of the study.

The summary of the follow-up assessment activities is reported in Table 2.

**Table 2 Tab2:** Baseline, Follow-up activities and Data to be collected summary

Follow-up time	Activity	Documentation
Week 0 (Baseline)	• Socio-demographic questionnaire • Fagerstrom test for nicotine dependence • WHO quality of life (QOL) instrument	• Age of first use, duration of use, amount used, mental illness managed, other substances used • Fagerstrom test score • WHO QOL score
Week 4	• Explored progress made and documented quit attempts • Focused on challenges experienced and how they were managed • Documented number of sticks currently smoked • Those reporting complete cessation and who gave consent for saliva testing, were then screened using cotinine test	• Quit attempts made • Amount currently being smoked • Cotinine test
Week 12	• Explored progress made and documented quit attempts • Focused on challenges experienced and how they were managed • Documented number of sticks currently smoked • Those reporting complete cessation and who gave consent, were screened using cotinine test	• Quit attempts made • Amount currently being smoked • Cotinine test
Week 26 (Final follow-up)	• Explored progress made and documented quit attempts • Focused on challenges experienced and how they were managed • Documented number of sticks currently smoked • Those reporting complete cessation, gave consent, then were screened using cotinine test • Administered WHO QOL instrument	• Recorded quit attempts made • Amount currently being smoked • Cotinine test • WHO QOL score

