### Outcome measures

The study’s primary outcome was self-reported continuous tobacco use abstinence, biochemically verified, at Week 26. It was estimated that the intervention would increase tobacco cessation from the current rate of 15 to 35% [21]. While adjusting for 30% attrition rate, with a sample size of 48 per group, 96 participants would provide 80% power to detect this between-group difference with a two-sided alpha = 0.05.

Secondary outcomes assessed included cessation at Week 4 and 12, number of quit attempts, reduction in number of cigarettes used per day, and health-related quality of life measured at Week 26.

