During exploratory data analysis, discrete variables will be summarized using frequencies and percentages, while continuous variables will be summarized using measures of central tendency and dispersion such as means with standard deviations and median with inter-quartile ranges, where appropriate. Bivariate analysis will be carried out to compare the intervention groups with the control groups with respect to socio-demographic characteristics, history of tobacco and substance abuse, type(s) of mental illness, and WHOQOL-100 scores at baseline. Mann Whitney tests will be employed to compare the intervention and control groups where predictor variables are continuous, and chi-squared tests will be applied when the predictor variable is categorical. We will compare unadjusted and adjusted cessation rates at 6 months, recognizing the limitations of the study design at eliminating potential confounders between the two groups given the non-randomized nature of group allocation. Potential confounders include age, sex, baseline tobacco, and baseline type of mental illness, among others. Time to cessation of tobacco use will be compared between the two groups by creating Kaplan-Meier curves and with the creation of corresponding Cox proportion hazard models to determine the effect of the intervention on the primary study outcome. We will report unadjusted and adjusted models, the latter which will aim to control for independent factors associated with relapse. We will perform similar analyses for secondary outcomes as well. All analyses will be carried out using IBM SPSS Statistics Software Version 24, and a two-sided *p* < 0.05 will be used to determine statistical significance.

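### The Cox model of time to cessation is the analysis tied to the primary outcome, but that outcome is a yes/no status at Week 26; the planned 6-month rate comparison fits it and is not named as primary

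*Protocol article*

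**What the plan says.** **The outcome.** Under Outcome measures, the "primary outcome was self-reported continuous tobacco use abstinence, biochemically verified, at Week 26". The abstract also describes a status at a fixed time: "The primary outcome was tobacco cessation at 24 weeks, measured through cotinine strips". (Week 24 against Week 26 is a separate inconsistency.) Cessation at the earlier visits is kept apart: "Secondary outcomes assessed included cessation at Week 4 and 12, number of quit attempts".

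**The sample size.** The Sample size calculation section compares two proportions, 35% and 15%. Outcome measures states the power for that same difference.

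**The analysis.** Data management and analysis contains two comparisons of cessation:

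- "We will compare unadjusted and adjusted cessation rates at 6 months", followed by a list of potential confounders.
- "Time to cessation of tobacco use will be compared between the two groups by creating Kaplan-Meier curves" together with "Cox proportion hazard models to determine the effect of the intervention on the primary study outcome". The models are reported unadjusted and adjusted, "the latter which will aim to control for independent factors associated with relapse".

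**The timing.** Under Baseline and follow-up assessments: "During weeks 4, 12 and 26, Quit attempts made, amount currently being smoked and Cotinine test results were documented".

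**The concern.** Only the Kaplan-Meier/Cox sentence ties a method to the primary outcome by name, and its time variable is not that outcome. The outcome asks whether a participant is verified as continuously abstinent at Week 26. A time-to-cessation model asks how soon participants reach a cessation event, and the event is not defined. If it is first cessation, a participant abstinent at Week 4 and using tobacco again at Week 12 is an event in the model and a failure on the outcome. Relapse is mentioned only in choosing adjustment factors; no rule makes it cancel an event.

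At stake is the efficacy conclusion. Two analyses are planned at two-sided 0.05, they can point in different directions, and the text attaches the primary-outcome claim to the one that does not measure that outcome.

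**Working it through.** **1. The plan's own figures.** The sample-size table gives 35% v 15% and an odds ratio of 3.05. Check: (0.35/0.65)/(0.15/0.85) = 3.05, which reproduces. The inputs are two proportions; no hazard ratio or event count appears. (The stated 37 per group does not follow from the printed formula, which gives 2 × 0.25 × 0.75 × 7.849 / 0.20² = 73.6. That is a separate matter and nothing below depends on it.)

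**2. Linking the two analyses.** Let e be the proportion who ever stop and r the proportion of those who relapse before Week 26. Then:

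- Week 26 abstinence = e × (1 − r).
- Hazard ratio for first cessation, under proportional hazards = ln(1 − e₁)/ln(1 − e₀), with 1 = intervention and 0 = control.

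The hazard ratio does not contain r; the Week 26 outcome does. The documents give neither e nor r, so every row below is an assumption. The 15% and 35% are the plan's own.

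| Ever stop (int. v control) | Relapse (int. v control) | Week 26 abstinence | Hazard ratio |
|---|---|---|---|
| 40% v 20% | 62.5% v 25% | 15% v 15% | ln 0.60/ln 0.80 = 2.29 |
| 60% v 30% | 75% v 50% | 15% v 15% | ln 0.40/ln 0.70 = 2.57 |
| 50% v 50% | 30% v 70% | 35% v 15% | 1.00 |
| 45% v 45% | 22% v 67% | 35% v 15% | 1.00 |
| 70% v 30% | 50% v 50% | 35% v 15% | ln 0.30/ln 0.70 = 3.38 |
| 35% v 15% | none | 35% v 15% | ln 0.65/ln 0.85 = 2.65 |

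At the same design effect of 35% v 15%, the hazard ratio runs from 1.00 to 3.38. With no Week 26 effect it can be 2.29 or 2.57.

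**3. Rejection rates.** Simulation with 50 per arm, independent participants, no dropout, first cessation seen at Week 4, 12 or 26, 4,000 trials per scenario and two-sided 0.05. The log-rank test (the Cox score test) is set against a pooled two-proportion test at Week 26. Ranges cover repeated runs with different splits of the event times over the visits.

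| Scenario | Log-rank | Week 26 test |
|---|---|---|
| 15% v 15% at Week 26; ever stop 30% v 20% | 21–22% | 5–6% |
| 15% v 15%; ever stop 35% v 20% | 40–41% | 5–6% |
| 15% v 15%; ever stop 40% v 20% | 59–61% | 5–6% |
| 35% v 15%; ever stop 45% v 45% | 4–5% | 65–66% |
| 35% v 15%; no relapse | 63–64% | 63–64% |
| 15% v 15%; ever stop 30% v 30%, equal relapse | about 5% | 5–6% |

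The first four rows have relapse differing between arms, and there the tests part. In the last two rows it does not differ, and they agree.

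**4. Ties.** Event times sit on three values in every scenario, yet the log-rank test rejects in about 5% of trials when the ever-stop rates are equal. The simulation therefore shows no harm from ties alone.

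**The case against.** The strongest reply is that a suitable analysis is already planned. The 6-month cessation rates, unadjusted and adjusted, are a comparison of the binary outcome, and the sample size rests on proportions. A programme that produced only short quits would show no difference there. A reader might infer that Cox is the only efficacy analysis, or that such a programme would be reported as effective. The documents do not support either: it could be so reported, if the Cox result took precedence. What remains is that the rate comparison is not called primary while the Cox model is given that role.

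Second, a reader might state as fact that relapsers count as successes. The event is undefined. Since the outcome is continuous abstinence, the event could be the start of abstinence held to Week 26, and relapsers would then not be events. An article may leave event definitions to a fuller document. This makes the relapse argument conditional. It does not remove the stated mismatch: even on that reading, a Cox model also weighs how early abstinence began.

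Third, the reversals need strongly differential relapse, such as 62.5% v 25% or 22% v 67%, and nothing in the documents supports such figures. This stands. It might also be argued that the later sessions aim at preventing relapse, so that differential relapse is likely. The section on group sessions 7–9 describes discussion of feelings, cessation attempts and challenges, with supportive therapy, and does not name relapse prevention.

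Finally, three tied event times might be thought to rule out a Cox model. No harm from that was shown, so a discrete-time model is an option and not a requirement.

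**Conclusion.** The concern holds as a mismatch between the stated primary outcome and the method tied to it by name, combined with no ranking of two planned analyses. It is visible in the text and does not depend on what an unseen analysis plan might add.

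Its numerical size cannot be fixed from the documents. On the first-cessation reading and under assumed rates, the hazard ratio can be about 2.3 with identical Week 26 abstinence, or 1.0 with the full design difference of 35% v 15%. The analyses agree if nobody relapses. With equal relapse they point the same way, though the hazard ratio need not have the same size. The conclusion can therefore reverse only if relapse differs between arms, which the plan neither excludes nor quantifies. That possibility, and the low cost of removing it, make the correction worth requiring.

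**What to change.** In Data management and analysis:

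1. Name the already planned 6-month comparison as the sole primary analysis, and state that it uses the proportions with verified continuous abstinence at Week 26. Report the risk difference with a 95% confidence interval, plus an adjusted binary model on the same outcome.
2. Delete from the Kaplan-Meier/Cox sentence the clause that claims to determine the effect on the primary outcome.
3. Label that analysis as a secondary, descriptive analysis of time to first cessation, and say what counts as the event. Note that verified status is known only at Weeks 4, 12 and 26. A discrete-time model or explicit handling of ties is optional.

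**Cost.** A wording change and a simple binary model on data already collected. The downside is that the hazard ratio can no longer be offered as the main result. Because the Current status section gives follow-up as complete, the change should say whether it was made before results by arm were seen.

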### Objectives

To determine the efficacy and safety of a group tobacco cessation behavioral intervention among tobacco using patients with mental illnesses on tobacco cessation at 6 months.To evaluate the impact of tobacco cessation on health-related quality of life of patients with mental illnesses.

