#### Group sessions 7–9 (weeks 14–26)

Participants continued attending the CSAT outpatient and ward follow-up programs during this period. Behavioral group sessions 7–9 (weeks 14–26) were conducted once a month by the facilitators whereby each session was begun with a round of discussion on how participants were feeling about their cessation attempts, including any challenges they had experienced. The self-reported amount of tobacco used and quit attempts were documented. The study team also documented the challenges raised and tried to offer practical and supportive therapy for the challenges.

Summary of the group sessions and topics can be found in Table 1.

**Table 1 Tab1:** Group sessions and topics summary

Time Frame	Group sessions
After signed consent	5 As Ask- History of tobacco use Advice- On need to quit tobacco use, and inform on effects of tobacco use Assess- On readiness to quit tobacco use, if not ready use motivational skills to increase readiness Assist- Offer intervention support. Inform on behavioral coping skills and available pharmacotherapies Arrange- Arrange date, time and place of next session to introduce coping skills)
Session 1 (Week 1)	7. Introduction to the program and reasons to quit tobacco use
Session 2 (Week 3)	8. Benefits of quitting and understanding why we smoke and ways of quitting 9. setting quit date
Session 3 (Week 5)	10. Withdrawal symptoms and social support
Session 4 (Week 7)	11. Dealing with stress and anxiety and coping with depression
Session 5 (Week 9)	12. Assertiveness training and anger management
Session 6 (Week 11)	13. Tobacco-free lifestyle and dealing with high risk situations
Follow up sessions (Weeks 14–26)	14. Round of discussion on participants’ feelings, cessation attempts, challenges experienced, and how they coped 15. Documentation of self-reported quit attempts 16. Supportive therapy

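### The plan carries cessation-rate and survival methods over to secondary outcomes they do not fit, and states no baseline adjustment for Week 26 quality of life

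*Protocol article*

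**What the plan says.** The section on data management and analysis of the protocol article first sets out the cessation analysis: "We will compare unadjusted and adjusted cessation rates at 6 months". It then turns to survival methods: "Time to cessation of tobacco use will be compared between the two groups by creating Kaplan-Meier curves", with Cox models. On covariates it says: "We will report unadjusted and adjusted models, the latter which will aim to control for independent factors associated with relapse". The secondary outcomes get one sentence, directly after this: "We will perform similar analyses for secondary outcomes as well".

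Under Outcome measures, the secondary outcomes are cessation at Weeks 4 and 12, number of quit attempts, and "reduction in number of cigarettes used per day, and health-related quality of life measured at Week 26". WHOQOL is taken at baseline, and "During week 26, the WHOQOL questionnaire was re-administered". Amount of tobacco used is also recorded at baseline. The second objective reads: "To evaluate the impact of tobacco cessation on health-related quality of life of patients with mental illnesses".

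**The concern.** Three of the secondary outcomes are a score, a count and a change in an amount. The methods that precede the sentence on secondary outcomes are for a yes/no outcome or for a time to an event. An analyst who follows the text has no usable instruction for these three, and must choose a method once the data are in hand.

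The covariate set carried over is also unsuited to quality of life. It is meant to capture relapse, whereas the strongest candidate predictor of a Week 26 WHOQOL score is normally the same person's baseline score. The article itself concedes that allocation was not randomized, so a baseline difference between arms is a live possibility. If the Week 26 scores are compared without the baseline score, part of any such difference appears as an effect of the intervention, and the comparison is less precise than the collected data allow.

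**Working it through.** **Fit of method to outcome.** The plan gives no figure to reproduce here, so the text is set side by side. The sentence on secondary outcomes has two possible antecedents.

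| Secondary outcome | Type | Adjusted cessation rate (binary) | Kaplan-Meier/Cox (event and time) |
|---|---|---|---|
| Cessation at Weeks 4 and 12 | yes/no | fits | can feed a time-to-cessation analysis |
| Quit attempts | count | does not fit | does not fit |
| Reduction in cigarettes per day | change in amount | does not fit | does not fit |
| WHOQOL at Week 26 | score, one follow-up value | does not fit | does not fit |

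The same section names Mann-Whitney and chi-squared tests. They come straight after the list of baseline comparisons and are worded for predictor variables, so they do not clearly supply a method for follow-up outcomes.

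**Use of baseline values.** Baseline WHOQOL appears twice in the analysis section: as a descriptive item and in the between-group comparison at baseline. It is not among the named confounders, which are age, sex, baseline tobacco and baseline type of mental illness, although that list is left open. Baseline tobacco is thus covered by name; baseline WHOQOL is not.

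**What baseline adjustment of WHOQOL is worth.** The documents give no correlation r between baseline and Week 26 scores, so r = 0.5 to 0.7 is an assumption. Group size is 50 (abstract); 30% attrition (Outcome measures) leaves 50 × 0.70 = 35. Clustering by the recruitment groups of 10 is ignored.

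- Residual variance after adjustment, relative to ignoring baseline, is 1 − r². At r = 0.5 this is 1 − 0.25 = 0.75, so 25% is removed. At r = 0.7 it is 1 − 0.49 = 0.51, so 49% is removed.
- Equivalent sample size is 1/(1 − r²): 1/0.75 = 1.33 and 1/0.51 = 1.96, or 33% to 96% more participants for the same precision.
- Detectable difference in SD units, with 80% power and two-sided 0.05, is (1.960 + 0.842) × √(2/n) × √(1 − r²).

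| n per group | Baseline ignored | r = 0.5 | r = 0.7 |
|---|---|---|---|
| 50 | 0.56 | 0.485 | 0.40 |
| 35 | 0.67 | 0.58 | 0.48 |

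- Carry-over of imbalance: if the arms differ by d SD at baseline and the SD is the same at both times, an unadjusted Week 26 comparison is shifted by about r × d. At the assumed r, that is half to seven tenths of the baseline difference.

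**Limit of that figure.** It applies to WHOQOL. A reduction in cigarettes already uses the starting amount. A change score has variance 2(1 − r) in the same units, so the gain from adjusting instead of subtracting is 2/(1 + r) − 1: 33% at r = 0.5 and 18% at r = 0.7.

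**Quit attempts.** Group session notes in the intervention arm also record them; for the later sessions, "The self-reported amount of tobacco used and quit attempts were documented". Table 2 places quit-attempt documentation at Weeks 4, 12 and 26, and the controls' questionnaires fall at the same three times. The outcome definition does not say which records count.

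**The case against.** The strongest reply is that the word similar may mean no more than unadjusted plus adjusted comparisons, with a model suited to each outcome, and that a condensed article may leave the model names to a fuller document. The first part stands: the text is not a firm commitment to Cox regression, and a reader who infers that survival models are definitely planned for WHOQOL goes beyond it. The second part stands only in part. The article does not stay silent; it points to the preceding analyses, and neither of those suits three of the secondary outcomes.

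Four further inferences are tempting and are not supported:

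- *Baselines are ignored altogether.* Baseline tobacco is a named confounder in an open list, adjusted models are planned, and a reduction in cigarettes needs a starting amount. The gap that remains is that no adjustment for baseline WHOQOL is stated.
- *Quit attempts will be inflated in the intervention arm because they were asked about more often.* Recording is described for sessions 2 to 9, so at most 8 + 3 = 11 occasions against 3, about 3.7-fold. But nothing says that session notes enter the outcome, and Table 2 points to the three common times. The documents show an undefined source, not a bias.
- *The 33% to 96% gain covers every outcome.* It does not hold for a change in cigarettes per day, as shown in the working.
- *A comparison of quitters with non-quitters is planned.* The second objective, read literally, asks about the effect of cessation itself, but no such analysis is specified, and quality of life is listed as an ordinary secondary outcome of the trial.

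**Conclusion.** The point holds in a limited form. The sentence on secondary outcomes is ambiguous, and on either reading of what precedes it, the method does not fit Week 26 WHOQOL, quit attempts or reduction in cigarettes per day. No analysis of Week 26 WHOQOL adjusted for its baseline is stated, although the baseline score is collected and allocation was not randomized. At an assumed correlation of 0.5 to 0.7, leaving it out forgoes a 25% to 49% reduction in WHOQOL variance; with 50 per group the detectable difference is 0.56 SD instead of 0.485 to 0.40 SD. The misfit of method to outcome type rests on the text alone; the size of the precision loss rests on the assumed correlation and ignores clustering. The primary outcome and cessation at Weeks 4 and 12 are not touched.

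**What to change.** Replace the sentence on secondary outcomes with one method for each:

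- **WHOQOL at Week 26:** linear model on arm, with baseline WHOQOL as covariate plus the named confounders.
- **Cigarettes per day at Week 26:** linear model on arm, with baseline amount as covariate.
- **Quit attempts:** a count model, or another method suited to counts, using only the Weeks 4, 12 and 26 records common to both arms.
- **Cessation at Weeks 4 and 12:** the method used for the primary outcome.

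State that the quality-of-life comparison is between allocated arms, and label any comparison of quitters with non-quitters under the second objective as observational.

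The cost is wording; the article lists all the variables as collected. Session-level quit attempts in the intervention arm become descriptive. Under Current status, follow-up had ended and results were still awaited, so the change should be dated and reported as made after follow-up closed.
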